### 3.3. Intervention and Comparator

This is a non-randomized study, including all patients diagnosed with HPV+ OPSCC. Samples will be collected from included patients at the time of diagnosis (baseline), at the follow-up visit two months after completion of treatment, and every six months thereafter for a minimum of two years and up to three years. Each sample will be analyzed for the presence of ctHPV-DNA corresponding to the HPV genotype identified in the patient’s primary tumor. If a sample is positive after completion of treatment, the patient will be referred for a clinical examination at the Department of Otolaryngology, Head and Neck Surgery and Audiology, Copenhagen University Hospital—Rigshospitalet, followed by a PET/CT scan (supplemented by MRI if a tumor is clinically visible in the head and neck region) within 12 weeks.

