**Figure 1 diagnostics-16-02169-f001:**

Overview of the blood sampling schedule. The first blood sample is drawn at the time of diagnosis (baseline) to assess baseline cfHPV-DNA levels before treatment initiation. The second blood sample is drawn at the first follow-up visit, two months after completion of treatment. The third blood sample is drawn six months after completion of treatment, and subsequent blood samples are collected every six months for up to three years after completion of treatment.

If a blood sample is positive at any time point after completion of treatment, the patient will be referred for a clinical examination at the Department of Otolaryngology, Head and Neck Surgery and Audiology, Copenhagen University Hospital—Rigshospitalet, followed by a PET/CT scan (supplemented by MRI if a tumor is clinically visible in the head and neck region) within 1–2 weeks. If no recurrence is detected during these examinations, blood sampling will be repeated after three months. If the additional blood sample is positive for ctHPV-DNA, a second clinical examination and PET/CT scan will be performed. If recurrence is still not detected at the additional follow-up visit, the patient will return to the standard follow-up schedule (Figure 2).

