## 5. Methods: Assignment of Interventions

### 5.1. Randomization

This study is non-randomized. All included patients will follow the same follow-up program, with blood samples collected at the same intervals as the standard clinical follow-up program for a minimum of two years and up to three years.

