### 5.2. Blinding

No blinding is performed. Results of each ctHPV-DNA analysis will be communicated to the treating physician, the patient, and the study investigators.

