### 6.3. Statistical Methods

The primary outcome, namely the sensitivity and specificity of ctHPV-DNA for detecting recurrence, will be calculated with 95% confidence intervals. Sensitivity will be determined among patients who develop recurrence, and specificity among patients who remain recurrence-free during follow-up. Positive predictive value will be determined among patients with positive ctHPV-DNA samples, and negative predictive value among patients with negative ctHPV-DNA results.

Only recurrence confirmed by a clinical and/or radiological examination will be regarded as recurrence. Histopathological confirmation will be included in the clinical verification if tissue sampling is feasible during the clinical examination.

The primary analyses will include all enrolled patients with a ctHPV-DNA baseline blood sample and at least one post-treatment blood sample, and follow-up assessment. Patients will be analyzed according to their clinical follow-up data, irrespective of the completeness of subsequent blood sampling or imaging, to minimize bias and reflect a real-world clinical practice.

Time-to-event outcomes, including time to recurrence detected by ctHPV-DNA and time to recurrence detected by clinical and/or radiological examination, will be analyzed using Kaplan–Meier survival curves. Median time to recurrence and corresponding 95% confidence intervals will be reported. Comparisons between ctHPV-DNA detection and standard surveillance will be performed using the log-rank test.

Healthcare utilization endpoints, including the number of PET/CT scans and Cancer Fast-Track referrals without evidence of recurrence, will be summarized using descriptive statistics (mean, median, standard deviation, and interquartile range). Between-group comparisons (e.g., patients with versus without recurrence) will be performed using *t*-tests for normally distributed variables or Mann–Whitney U tests for non-parametric distributions.

Analyses will use all available data, and, where appropriate, missing data will be handled using multiple imputation under the assumption that data are missing at random (MAR).

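### The planned log-rank test treats two detection times from one cohort as independent groups, and for test-triggered recurrences the clinical date depends on the ctHPV-DNA result

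*Protocol article*

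**What the plan says.** Section 6.3 defines two time-to-event outcomes: "time to recurrence detected by ctHPV-DNA and time to recurrence detected by clinical and/or radiological examination, will be analyzed using Kaplan–Meier survival curves". It continues: "Median time to recurrence and corresponding 95% confidence intervals will be reported". It then names the comparison: "Comparisons between ctHPV-DNA detection and standard surveillance will be performed using the log-rank test".

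The design has one group. Section 5.1 states: "This study is non-randomized. All included patients will follow the same follow-up program, with blood samples collected at the same intervals". No parallel, external or historical control is described.

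The test result drives the clinical work-up. The text with Figure 1 states: "If a blood sample is positive at any time point after completion of treatment, the patient will be referred for a clinical examination", with PET/CT to follow. Section 5.2 adds: "No blinding is performed. Results of each ctHPV-DNA analysis will be communicated to the treating physician, the patient, and the study investigators". Section 6.3 counts a recurrence only when a clinical and/or radiological examination has confirmed it.

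The aim in Section 1.2 is to detect recurrence earlier than, or together with, conventional assessment. Section 3.4 makes sensitivity and specificity the primary endpoint and lists the two times to recurrence as secondary.

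**The concern.** Three things do not fit together.

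1. **Pairing.** The log-rank test assumes independent groups. Here both curves are drawn from the same patients, most of whom are censored at the same moment on both.
2. **Comparator date.** When a positive sample leads to the examination that verifies the recurrence, the clinical date is a product of the test. It is not the date on which standard surveillance would have found the disease, so calling that curve standard surveillance mislabels it.
3. **Median.** If about one patient in nine recurs, a Kaplan–Meier curve for the whole cohort stays far above 0.5.

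This is the only formal comparison of timing in the plan. A non-significant p-value from it could be read as evidence that ctHPV-DNA testing finds recurrence no earlier, when the test could hardly have given any other answer.

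**Working it through.** **Inputs from the protocol article.** Target 200 patients, minimum 167; prevalence 11%; expected sensitivity and specificity 95%; margin 10% (Section 4.1). Recurrence 10–15%; previous lead up to four months (Section 1.1). Median time to recurrence 12–18 months; follow-up two to three years (Section 4).

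**The plan's own figure.** No sample size or power is stated for the log-rank test. The accuracy calculation reproduces: 1.96² × 0.95 × 0.05 / 0.10² = 18.25 diseased, and 18.25 / 0.11 = 165.9, so 166 against 167 stated. Expected recurrences are 167 × 0.11 = 18.4, or 200 × 0.11 = 22 at the target size.

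**A bound by hand.** Take 200 patients and 22 verified recurrences, all within the first two years, with no earlier censoring. Let the ordering favour the test as far as possible: all 22 ctHPV-DNA detections come before the first clinical verification.
- Observed ctHPV-DNA events: 22.
- Expected, over the 22 ctHPV-DNA event times: the sum of (200 − i)/(400 − i) for i = 0 to 21, which is 10.70.
- Expected, over the 22 clinical event times: the sum of 178/(378 − j) for j = 0 to 21, which is 10.66.
- O − E = 22 − 21.36 = 0.64. The variance is the sum of n₁n₂/n² over the 44 event times, 10.99, with square root 3.31.
- z = 0.64 / 3.31 = 0.19, against the 1.96 needed.

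Both curves end with the same 22 events among the same 200 patients, so the statistic has almost nothing to respond to. With 30 recurrences (15%) the same calculation gives z = 0.31.

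**Simulation.** 200 patients, 11% recurrence, 800 runs per setting. Assumptions not in the protocol: log-normal recurrence times with median 15 months, normal lead with SD 2 months, uniform censoring at 24–36 months, every recurrence detected by both methods.

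| Mean lead | Log-rank, full cohort | Log-rank, recurrers only | Paired signed-rank, full-cohort / recurrers-only runs |
|---|---|---|---|
| 0 | 0% | 0% | 4.8% / 4.4% |
| 2 months | 0% | 0.25% | 99% / 98% |
| 4 months | 0% | 13% | 100% / 99.9% |
| 0.35 months (SD 0.1; referral delay only) | 0% | 0% | 100% / 100% |

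At zero mean lead the variance of z is 0.014 in the full cohort (SD √0.014 = 0.12) and 0.082 among recurrers (SD 0.29), where a valid test has 1. Two further simulations with 95% of recurrences detected and mean leads of 2, 4 and 6 months also gave 0% in the full cohort, with null SDs of 0.12 and 0.18. Among recurrers they gave 0.1%, 6% and 19% in one, and 0.5%, 14% and 37% in the other.

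**Comparator date.** The last row of the table uses 10.5 days / 30.4 = 0.35 months, the middle of the one to two weeks given with Figure 1. A paired test is then significant in every run from referral delay alone. Section 3.3 gives another delay: "followed by a PET/CT scan (supplemented by MRI if a tumor is clinically visible in the head and neck region) within 12 weeks", which is 84 / 30.4 = 2.8 months. The two passages must be reconciled, because this delay is much of what the gap measures.

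**Median.** With 10–15% recurrence the whole-cohort curve ends near 0.90 to 0.85. The probability of at least 100 events in 200 patients is about 1 × 10⁻⁴² at 11% and 4 × 10⁻³¹ at 15%. Counting every positive patient as a ctHPV-DNA event gives 0.11 × 0.95 + 0.89 × 0.05 = 14.9%. If the 5% false-positive rate applied to each of 5 to 7 samples, the total would be 31–37%, still below half.

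**The case against.** The strongest reply is about weight. The times are secondary endpoints, the study is sized on sensitivity and specificity, and no stopping or management decision depends on the log-rank result. All of that stands. A reader might infer that the main results are compromised; the protocol does not support this.

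Other stronger readings also fail:
- **That no median can exist.** Section 4 uses median time to recurrence in a sense that only works among recurrers, and there a median does exist. But Section 6.3 does not state that restriction, and the result would be conditional on recurring.
- **That the log-rank test must be non-significant.** This depends on counting only verified recurrences, which Section 6.3 favours. If 5% false-positive patients also counted as ctHPV-DNA events, simulated rejection was about 6–13%. At 5% per sample it was 100%, with or without lead time. Those rejections would reflect false positives, not earlier detection.
- **That the data say nothing about timing.** Recurrences found through symptoms or a routine visit without a prior positive test have clinical dates not set by the test. Those verified only after a first negative work-up have dates not fixed by the first positive alone.
- **That a paired or sign test is the cure.** In test-triggered cases the sample precedes the work-up by construction, so either test can be significant with no gain over standard follow-up.

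It is also fair that the simulated leads are free assumptions without a visit grid. The hand bound does not use them.

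**Conclusion.** The concern holds in this form. The log-rank comparison is wrong as written: it applies an independent-groups variance to paired times (null z SD about 0.1–0.2 in the full cohort). With verified recurrences as events it has essentially no power: 0% at mean leads of 2–6 months in the full cohort and roughly 0–37% among recurrers. The low power in the full cohort follows from the protocol's own counts; the range among recurrers depends on assumed distributions.

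Separately, lead time over standard follow-up is not identified in test-triggered recurrences. This comes from the design, and no choice of test removes it. The whole-cohort median will not be reached at the protocol's recurrence rate.

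The secondary time endpoints and the earlier-detection part of the aim are affected. The primary accuracy estimates and the sample size are not.

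**What to change.** In Section 6.3:

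1. Delete the log-rank comparison and put no significance test in its place, neither a sign test nor a paired test.
2. Among verified recurrences, report the proportions that were ctHPV-DNA-triggered, found clinically at the same visit, found clinically before a positive test, or never ctHPV-DNA positive, each with an exact 95% CI.
3. Report the interval from first positive sample to verification descriptively (median, range, CI), split by whether verification was triggered by the test or by symptoms or a routine visit. State that lead time is not identified in test-triggered cases.
4. Replace the whole-cohort median by cumulative incidence at 12, 24 and 36 months with death as a competing event. If a median among recurrers is wanted, say so and label it as conditional on recurrence.
5. Reconcile the two work-up delays in Section 3.3 and the text with Figure 1.

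The cost is small: wording, plus two recorded items, the verification date and the reason for each work-up. Section 6.1 lists recurrence status and imaging findings but neither of these explicitly; the secondary endpoints already imply both.

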## 2. Methods: Patient and Public Involvement, Trial Design

### 2.1. Patient and Public Involvement

The project was presented to the Danish Head and Neck Cancer Patient Association and received very positive feedback. The association has also contributed to drafting the written patient information to ensure clarity and readability.

To assess how the ctHPV-DNA test and its results influence patients’ quality of life, patients will be asked to complete the Danish version of the Fear of Cancer Recurrence Questionnaire (short form) [13,14] after receiving the result of each blood sample.

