### 3.4. Outcomes

The primary endpoint is to evaluate the sensitivity and specificity of ctHPV-DNA for the detection of recurrence in patients with HPV+ OPSCC, using clinically or radiologically verified recurrence as the reference standard. Time frame: A minimum of two years and up to three years after completion of primary treatment. Sensitivity will be calculated among patients who develop recurrence, whereas specificity will be calculated among patients who remain recurrence-free.

Secondary endpoints are defined as follows:Time to recurrence detected by ctHPV-DNA.Time to recurrence detected by clinical and/or radiological examination.Number of referrals to Cancer Fast-Track examinations based on a positive ctHPV-DNA test result without evidence of recurrence.Number of PET/CT scans performed because of a positive ctHPV-DNA test result without evidence of recurrence.

Quality of life (QoL), assessed using the Danish version of the Fear of Cancer Recurrence Questionnaire (short form), will be completed by patients after receiving the result of each blood sample.

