### 3.5. Harms

In general, blood sampling is considered a minimally invasive and simple procedure. When blood is drawn, transient pain at the venepuncture site and minor bruising may occur. This will pass within a few days. Patients participating in this study are covered by the Danish Patient Compensation Association (Patienterstatningen) in the event of study-related injury. The information leaflets “Forsøgspersoners rettigheder i sundhedsvidenskabelige forskningsprojekter” and “Før du beslutter dig” will be included with the written participant information [15,16]. Participants experiencing any adverse events that may be related to the study will be instructed to contact the study investigators.

Every patient with a positive ctHPV-DNA sample after completion of treatment will be referred for a PET/CT scan to assess whether there is evidence of clinical recurrence. The scan is a standard diagnostic PET/CT (2-(flourine-18) fluoro-2-deoxy-D-glukose (FDG)-PET/CT). During the PET part of the scan, the radioactive sugar FDG will be injected. PET has no known side effects. The CT part of the scan is performed using intravenous iodinated contrast medium. Immediately after injection, some patients may experience a transient sensation of warmth, a metallic taste, or an urge to urinate. As with any medicinal product, iodinated contrast medium carries a risk of allergic reactions upon injection. Approx. 5% of patients will experience minor side effects, including transient nausea, itching or rashes, whereas the risk of serious adverse reactions is very low (<0.1%). If the patient has previously experienced a severe reaction to IV contrast medium, the PET/CT can be conducted without the use of IV contrast medium. Some patients may experience claustrophobia during the scan, but trained staff will always be present to provide assistance if needed. Some participants may also undergo repeated PET/CT scans due to positive ctHPV-DNA blood samples and no evidence of recurrence, resulting in additional exposure to ionizing radiation. The associated risk is considered low, and only a small number of patients are expected to undergo more than one additional PET/CT scan.

Finally, patients with positive ctHPV-DNA blood samples but without evidence of recurrence may experience increased anxiety. However, this is expected to affect only a small number of patients, which is one of the reasons why the Fear of Cancer Recurrence Questionnaire has been included in the study.

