Sensitivity analyses will explore the impact of departures from the MAR assumption. For example, alternative imputation strategies may be applied, such as assuming that patients lost to follow-up either did or did not experience recurrence. These analyses will allow assessment of the robustness of estimates for sensitivity, specificity, time to recurrence, healthcare utilization, and patient-reported outcomes.

If the results from the sensitivity analyses are consistent with the primary analyses, confidence in the validity and generalizability of the findings will be strengthened. All statistical measures of uncertainty, including 95% confidence intervals and *p*-values, will be interpreted in the context of potential bias introduced by missing data.

Patient-reported quality of life (QoL), measured using the Danish version of the Fear of Cancer Recurrence Questionnaire (short form), will be evaluated as the change between follow-up visits. Each questionnaire item is rated on a five-point Likert scale (0–4) and summed into a total score. Total questionnaire scores will be reported, and within-patient changes will be assessed using the Wilcoxon signed-rank test. For repeated measurements over time, mixed-effects models using restricted maximum likelihood estimation will be employed, with patient ID as a random effect and time points as a fixed effect.

Exploratory analyses will include correlations between ctHPV-DNA levels and clinical outcomes, including recurrence, time to recurrence, and QoL scores. Spearman’s rank correlation coefficient will be used for non-parametric data. All tests will be two-sided, and a *p*-value < 0.05 will be considered statistically significant. All analyses will be conducted in R-studio.

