## 10. Discussion

This study protocol outlines a prospective investigation of the sensitivity and specificity of ctHPV-DNA testing for detecting recurrence in patients with HPV+ OPSCC. The study will be population-based, with all eligible patients diagnosed with HPV+ OPSCC in Eastern Denmark invited to participate. The goal is to enable earlier and more accurate detection of recurrence in this patient population. If ctHPV-DNA can reliably identify patients with recurrent disease at an earlier stage, it may facilitate timely and earlier clinical intervention while reducing unnecessary diagnostic procedures and their associated risks and side effects. Furthermore, patients diagnosed and treated at an earlier stage typically undergo less extensive treatment, which is associated with fewer permanent side effects than treatment for patients diagnosed with advanced disease.

Additionally, patients in post-treatment follow-up programs often worry about recurrence, which can significantly impact their quality of life. Currently, detection of a recurrence relies on the presence of symptoms or visible tumor recurrence during clinical examination. Clinicians can therefore only rule out clinically evident recurrence. The presumed high sensitivity of ctHPV-DNA testing for detecting recurrence may therefore provide patients with a greater sense of reassurance during follow-up and also provide clinicians with a reliable tool for recurrence detection. The main concern with ctHPV-DNA testing is the occurrence of positive ctHPV-DNA blood samples without evidence of clinical recurrence. This uncertainty could understandably increase patients’ anxiety. However, by including the Danish *Fear of Recurrence Questionnaire*, we will be able to assess how test results influence patients’ fear of recurrence throughout the study.

The existing literature on ctHPV-DNA in HPV+ OPSCC is limited by relatively small study populations, short follow-up, or only sporadic sampling during follow-up, and frequently focuses exclusively on HPV16-positive OPSCC [24,25,26,27,28,29,30]. This protocol addresses these limitations by including a large study population followed prospectively and systematically, with ctHPV-DNA blood sampling at baseline and at every follow-up visit after treatment completion, including clinical action on positive results. In addition, this study investigates a wide panel of HPV genotypes.

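### The fear-of-recurrence analyses fixed in Section 6.3 model time but not the ctHPV-DNA result, so they do not estimate the effect the questionnaire was included to measure

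*Protocol article*

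**What the plan says.** **Purpose.** Section 2.1 introduces the questionnaire with the words "To assess how the ctHPV-DNA test and its results influence patients’ quality of life". Section 10 repeats the aim: "we will be able to assess how test results influence patients’ fear of recurrence throughout the study". Section 3.5 states that "patients with positive ctHPV-DNA blood samples but without evidence of recurrence may experience increased anxiety", and gives this as one reason among several for including the instrument.

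**Timing.** Under Section 3.4 the questionnaire "will be completed by patients after receiving the result of each blood sample". Each score can therefore be tied to a known result.

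**Analysis.** Section 6.3 says the score "will be evaluated as the change between follow-up visits". It names a Wilcoxon signed-rank test for within-patient change. For repeated measurements it names a mixed model fitted by restricted maximum likelihood, "with patient ID as a random effect and time points as a fixed effect". A later paragraph of the same section lists exploratory correlations of ctHPV-DNA levels with several outcomes, QoL scores among them, using Spearman's coefficient for non-parametric data.

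**The concern.** The question is about results: does being told that a sample is positive, above all when no recurrence is then found, raise fear of recurrence? The two main analyses answer a different question, namely how the cohort's average score moves from visit to visit. Fear of recurrence may drift with time since treatment whatever the test shows, and a time coefficient cannot separate that drift from the effect of a result.

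Most results will be negative, so the visit averages mainly describe patients with negative results. The psychological harm that Section 3.5 anticipates would have no estimate and no confidence interval in the main analyses.

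**Working it through.** **1. Does any term carry the result?**

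| Analysis in Section 6.3 | What it estimates | Test result included? |
|---|---|---|
| Wilcoxon signed-rank | within-patient change between visits | no |
| Mixed model | mean score at each time point | no; time is the only fixed effect |
| Exploratory Spearman correlation | association of ctHPV-DNA level with score | level only |

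The correlation does not close the gap. It uses the measured level, not the positive or negative result the patient was told. No handling of repeated measures is stated. It also does not separate positives with recurrence from positives without, and fear would be expected to differ between those two groups.

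**2. The plan's own figure.** Section 4.1 gives sensitivity 95%, specificity 95%, prevalence 11%, margin 10% and a minimum of 167 patients.
- 1.96² × 0.95 × 0.05 / 0.10² = 18.25 patients with disease
- 18.25 / 0.11 = 165.9, so 166 against the stated 167

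This reproduces to within one patient. The point does not depend on it.

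**3. How many patients would ever test positive after treatment?** Assumption: the planning sensitivity and specificity apply per patient, not per sample.
- With recurrence: 167 × 0.11 × 0.95 = 17.5
- Without recurrence: 167 × 0.89 × 0.05 = 7.4
- Total: 24.9, about 25 of 167 (at N = 200: 20.9 + 8.9 = 29.8, about 30)

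**4. Dilution.** The Figure 1 legend implies post-treatment samples at 2, 6, 12, 18 and 24 months, with 30 and 36 months at most, so 5 to 7 per patient. Counting one positive questionnaire per ever-positive patient:
- All positives: 24.9 / (167 × 7) = 2.1% to 24.9 / (167 × 5) = 3.0%
- Positives without recurrence: 7.4 / 1169 = 0.6% to 7.4 / 835 = 0.9%

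The documents give no effect size. Per point of assumed rise after a positive, the overall mean score moves by 0.02 to 0.03 points. An assumed 5-point rise moves it by 0.11 to 0.15, and an 8-point rise by 0.17 to 0.24. For positives without recurrence alone, a 5-point rise moves it by 0.03 to 0.04. Persistent positives, and the three-month repeat sample described in Section 4, would raise these shares somewhat. Clustering of positives at one visit would raise the shift at that visit.

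**5. Illustrative simulation.** Every value except the 167 patients and the planning rates is an assumption: 7 visits, between-patient SD 5, within-patient SD 4, positives spread evenly over visits, one positive per affected patient, 60 simulated trials per scenario.

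| True rise after a positive | Time-only model: joint time test rejects | Model with result: mean estimate | Model with result: rejects |
|---|---|---|---|
| 0 | 5% | −0.14 | 3% |
| 5 points | 8% | 4.99 | 100% |

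With 60 trials, 8% and 5% are 5 and 3 rejections, which cannot be told apart. The pooled Spearman correlation under the 5-point effect averaged about 0.11.

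**6. Precision of the added contrast**, under the same assumed SDs. Comparing one positive questionnaire with the mean of a patient's six others has variance 4² × (1 + 1/6) = 18.7 per patient.
- All positives: √(18.7 / 24.9) = 0.87, 95% half-width about 1.7 points
- Positives without recurrence: √(18.7 / 7.4) = 1.59, 95% half-width about 3.1 points

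**The case against.** **A reader might infer that nothing in the plan links ctHPV-DNA to the score.** That is too strong. Section 6.3 does plan the exploratory correlation. It is a weak substitute for the reasons given in step 1 of the working, but it exists.

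**A reader might infer that a flat time trend will be presented as reassurance.** No passage says so. The supported statement is narrower: a flat trend would be uninformative about the effect of a positive result.

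**A reader might take anxiety to be the main concern the protocol names.** Section 10 gives that place to positive samples without clinical recurrence, with anxiety as a possible consequence.

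**Description over time is not irrelevant.** Section 2.1 speaks of the test as well as its results, so how scores evolve under a testing programme has some interest. This stands, and is why time should stay in the model. It does not answer the part about results.

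**An analysis plan that is not shown could add the term, and the score is not the primary endpoint.** Both are fair and limit the weight of the point. But the article does not leave the model open. It states the estimation method, the random effect and the fixed effect, and these do not match the stated purpose.

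**Conclusion.** The point holds. The stated purpose concerns the influence of results, while the two main analyses are specified without the result and estimate average change over time. At the planning values, read per patient, about 25 of 167 patients would ever test positive after treatment, so positive results would precede only about 2 to 3% of post-treatment questionnaires, and those without recurrence under 1%. The dilution follows from the protocol's own rates and schedule. The size of any effect on the score is an assumption, and the simulation is an illustration, not a forecast. The primary endpoint is unaffected. This should be corrected because a named patient-reported aim would otherwise rest on an exploratory correlation alone.

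**What to change.** - **Model.** Keep time points and the patient random effect. Add the most recently communicated post-treatment result, positive versus negative, as a time-varying fixed effect.
- **Baseline.** If a questionnaire is collected after the pre-treatment sample, treat it as baseline and not as an exposure level. Section 9 reports 97.2% detection at diagnosis, so nearly all those samples will be positive.
- **Contrasts.** Report positive versus negative with a 95% CI first, then positive without verified recurrence versus negative. Examination and PET/CT follow the positive result, so assign recurrence status by what the patient had been told when completing the questionnaire, or label the split as retrospective.
- **Wilcoxon test.** It can stay, applied to scores before versus after the first positive result.
- **Correlation.** Keep it as exploratory.

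**Cost.** Results, recurrence status and scores are already to be collected. The extra work is a revised model statement, a rule for dating each questionnaire against the result and the work-up, and possibly recording those dates. The main downside is precision: the contrast for positives without recurrence rests on about 7 patients and its interval will be wide. The plan should say so in advance.
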